#### Secondary objectives

2.1.2

Secondary objective 1: To assess the effective referral rate of identified patients with elevated CV risk in OM to the CV risk hospital consultation.Secondary objective 2: To assess the rate of hospital CV risk consults that effectively took place after the referral by the OM physician.Secondary objective 3: To measure the performance of the simplified referral process for a CV risk consultation, through the assessment of therapeutic adherence, and impact on the CV risk profile 12 months after the intervention.Secondary objective 4: To estimate the levels of Lipoprotein (a) in patients.Secondary objective 5: To estimate the prevalence of CV risk factors in workers in the industrial/manufacturing companies in the municipality of São João da Madeira, using the AHA Life's 8 system.Secondary objective 6: To assess the effective referral rate of patients to the primary care consultation.Secondary objective 7: To assess the effective application of the implementation strategies in the CARDIOGAP + project.

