#### Implementation science framework

2.1.3

This protocol is informed by the RE-AIM framework (Reach, Effectiveness, Adoption, Implementation, Maintenance), used to plan and evaluate pragmatic, real-world health system interventions. Primary and secondary objectives relate to RE-AIM dimensions as follows: Reach is addressed through the proportion of eligible OM attendees identified and screened (secondary objectives 1–2); Effectiveness is addressed through change in CV risk profile at 12 months (secondary objectives 3–4); Adoption is addressed through the referral rate by OM physicians and participating companies (secondary objectives 1 and 6); Implementation is addressed through fidelity to the referral protocol and consultation attendance (secondary objectives 2 and 7); and Maintenance, while outside the 18-month observation window of this pilot, will be discussed qualitatively as a direction for future, longer-term evaluation.

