#### Sample size

2.2.2

Based on prior publications (7, 12, 13), it was estimated that up to 15% of the studied population has at least 1 of the inclusion criteria for referral (very high cardiovascular risk), so there is the expectation to perform 150 cardiovascular risk appointments in the first 6 months of the project (6–7 appointments/week, divided into two weekly periods of 4 h).

In this sense, instead of a sample size calculation, a precision estimation was calculated: for a confidence interval of 95%, a prevalence of 15% and 1000 persons included, a margin of error of 2.2% is estimated. This precision-based estimate addresses the primary objective and the descriptive prevalence outcomes (secondary objectives 1, 2 and 5), for which the expected sample provides adequate precision. As a pilot implementation study, CARDIOGAP + is not powered to test a pre-specified hypothesis regarding the magnitude of risk-factor change; these analyses are exploratory and hypothesis-generating, intended to inform the design and sample size of a future, adequately powered evaluation.

The sample size may be adjusted to the participation of physicians from Occupational Health and participating companies, with ULSEDV having the capacity to accommodate more referrals.

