#### Statistical methods

2.3.1

To address the multifaceted endpoints of this study (Table 3), a combination of statistical techniques will be employed. Descriptive statistics will be calculated to assess various CV risk factors. Continuous variables will be summarized using n, mean, median, standard deviation, minimum, maximum and 25th and 75th percentiles. Categorical variables will be summarized using frequency counts and percentages. Missing data will be reported using frequency counts and percentages and assessed for pattern and extent; where data are judged to be missing at random, multiple imputation will be used as the primary approach. Outliers will be identified using standard distributional criteria, and treated in consideration of their impact on the analysis.

**Table 3 T3:** Cardiogap + endpoints.

Endpoint Description
1. Proportion (%) of patients who meet the follow-up criteria for CV risk hospital consultation identified in OM consultation: Descriptive statistics will be used to calculate the percentage of patients who meet the follow-up criteria for CV risk hospital consultation over all patients attending OM consultations.
2. Proportion (%) of High CV risk individuals identified in OM consultation: Descriptive statistics will be used to calculate the percentage of High CV patients over all patients attending OM consultations.
3. Proportion (%) of Very High CV risk individuals identified in OM consultation: Descriptive statistics will be used to calculate the percentage of Very High CV patients over all patients attending OM consultations.
4. Proportion (%) of patients referred to Hospital CV Risk Consultation, overall and stratified by risk category: Descriptive statistics will be used to calculate the percentage of patients referred to Hospital CV Risk Consultation, reported (a) over allpatients meeting follow-up criteria, (b) over High CV risk patients only, and (c) over Very High CV risk patients only, identified in OM consultation.
5. Proportion (%) of Hospital CV Risk Consultation Participation after Referral by OM: Descriptive statistics will be used to calculate the percentage of individuals referred from OM consultations who participate in hospital CV risk consultations over all patients referred to hospital consultations.

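### The single precision figure (±2.2 points at n = 1000) is extended to secondary objectives 1 and 2, whose denominators are at most about 150; their margins are about ±5 to ±8 points for rates of 50% to 90%

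*Protocol article*

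**What the plan says.** Section 2.2.2 replaces a sample-size calculation with a precision estimate: "for a confidence interval of 95%, a prevalence of 15% and 1000 persons included, a margin of error of 2.2% is estimated". It is the only precision figure in the article, and the abstract names feasibility and precision as the basis for the sample size. The same section says the estimate "addresses the primary objective and the descriptive prevalence outcomes (secondary objectives 1, 2 and 5), for which the expected sample provides adequate precision".

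The section also supplies the size of the referral group. It estimates that "up to 15% of the studied population has at least 1 of the inclusion criteria for referral" and concludes that "there is the expectation to perform 150 cardiovascular risk appointments in the first 6 months of the project".

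Secondary objective 1 (section 2.1.2) is "To assess the effective referral rate of identified patients with elevated CV risk in OM to the CV risk hospital consultation". Its endpoint, number 4 in Table 3, is calculated over patients who meet the follow-up criteria, and again within the High and Very High risk groups. Secondary objective 2 corresponds to endpoint 5, "the percentage of individuals referred from OM consultations who participate in hospital CV risk consultations over all patients referred to hospital consultations". Endpoints 1 to 3, by contrast, are taken over everyone attending the OM consultation.

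**The concern.** The margin was calculated for one proportion (15%) and one denominator (1000 workers). The text then names two objectives with a different proportion and a much smaller denominator. Referral and attendance are the core implementation results of this pilot, and precision is the only statistical reason given for its size. A reader of section 2.2.2 would take it that these two rates will be known to within about two points, and might plan a later evaluation on that basis.

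The expected 150 appointments raise a related difficulty. The number equals 1000 × 15% with every eligible patient referred and every referred patient attending. Yet 15% is worded as a maximum, referral and attendance are what objectives 1 and 2 are meant to measure, and section 2.4 lists barriers to attendance.

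A secondary matter is independence. Workers are recruited through their companies, and the calculation has no allowance for that.

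**Working it through.** **Inputs from the protocol.** 95% confidence, p = 0.15, n = 1000, stated margin 2.2 points (section 2.2.2); up to 15% meeting the referral criteria (section 2.2.2); denominators from Table 3, endpoints 1 to 5. **Assumed, because the protocol does not give them:** the true referral and attendance rates, the split into High and Very High risk, company size and the intracluster correlation (ICC).

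**1. The stated figure.** Half-width = 1.96 × √(p(1 − p)/n) = 1.96 × √(0.15 × 0.85/1000) = 0.0221, or 2.2 points. It reproduces, and it fits the denominator of endpoint 1.

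**2. The denominators for objectives 1 and 2.** Patients meeting criteria: at most 1000 × 0.15 = 150. Patients referred: no more than that if referral follows the criteria.

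**3. Half-widths at those denominators**, same formula, in percentage points. The last column is the n = 150 value divided by 2.2.

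| True rate | n = 150 | n = 120 | n = 100 | n = 75 | n = 150 relative to 2.2 |
|---|---|---|---|---|---|
| 50% | ±8.0 | ±8.9 | ±9.8 | ±11.3 | 3.6 |
| 80% | ±6.4 | ±7.2 | ±7.8 | ±9.1 | 2.9 |
| 90% | ±4.8 | ±5.4 | ±5.9 | ±6.8 | 2.2 |
| 95% | ±3.5 | ±3.9 | ±4.3 | ±4.9 | 1.6 |

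The n = 120 column illustrates 80% referral of 150 (an assumption). The n = 75 column illustrates a risk stratum holding half of the 150 (also an assumption).

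**4. Where the gap closes at n = 150.** A half-width of twice 2.2 (4.4 points) requires p(1 − p) = 150 × (0.044/1.96)² = 0.0756, so p is about 92%. A half-width of 2.2 requires p(1 − p) = 150 × (0.022/1.96)² = 0.0189, so p is about 98%.

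**5. Secondary objective 5.** The denominator of 1000 is right, but the margin depends on the prevalence of each factor. At 50% it is 1.96 × √(0.25/1000) = ±3.1 points.

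**6. Number of appointments.** 1000 × 0.15 × 1.00 × 1.00 = 150. With assumed referral of 80% and attendance of 60%: 150 × 0.8 × 0.6 = 72. With 90% and 80%: 150 × 0.9 × 0.8 = 108.

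**7. Clustering, for the 15% prevalence.** Design effect = 1 + (m − 1) × ICC, where m is workers per company; the half-width is multiplied by its square root. With m = 10 and ICC = 0.005 the design effect is 1.045 and the margin ±2.3. With m = 50 and ICC = 0.05 it is 3.45 and the margin ±4.1. Over this assumed range the factor is about 1.0 to 1.9.

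**The case against.** Section 2.2.2 does not print ±2.2 beside objectives 1 and 2. It says precision is adequate, and ±5 to ±8 points may well be adequate for a descriptive pilot with no hypothesis or threshold on these rates. That is a fair limit on the criticism: the wider margins are not shown to be unacceptable. But the text rests adequacy on a calculation that does not apply to these outcomes, and it offers no other.

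Referral follows written criteria, so the referral rate could exceed 92%, and the gap would then be less than twofold. This stands for objective 1. It is harder to rely on for attendance, given the barriers in section 2.4.

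Section 2.1.3 links objectives 1 and 2 to the share of OM attendees identified and screened, which would suggest a denominator of 1000. Table 3 specifies what is calculated, and it uses the smaller groups.

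The protocol calls 150 an expectation, allows the sample to be adjusted and says the hospital can take more referrals. So 150 is not a fixed cap, but it still rests on the maximum prevalence with no losses.

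Two stronger readings are tempting. A reader might infer that all the stated precision is several times too good; it is not, because 2.2 is right under independence for the 15% prevalence endpoint, and the clustering figures depend wholly on assumed company sizes and ICCs. A reader might also infer that results by company, or cluster-adjusted intervals, cannot be produced because Table 2 has no company or OM-physician field. That is not established. Table 2 is not exhaustive: visit date and participant number are recorded (section 2.3) but not listed there. The choice of variance method may properly sit in the analysis plan.

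**Conclusion.** The statement in section 2.2.2 is wrong as written for secondary objectives 1 and 2. The calculation it cites is correct, but it belongs to a different proportion and a denominator nearly seven times larger (1000/150 = 6.7). The discrepancy of roughly 2 to 3.6 times at n = 150 comes from the denominator and the rate alone, and it assumes independent patients and true rates of 50% to 90%. Fewer referred patients, or reporting within the High and Very High groups, would widen the margins further.

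The 150 appointments are a best-case number at the planned enrolment and should be described that way. Clustering by company is a secondary caution: it may widen the intervals, but the protocol gives nothing from which to say by how much.

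**What to change.** Revise section 2.2.2 as follows.

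- Limit the 2.2-point margin to the 15% prevalence endpoint among all OM attendees, and say that it assumes independent workers. For objective 5, note that the margin varies with the prevalence of each factor.
- Give a separate margin for secondary objective 1 (n about 150; about ±5 to ±8 points for rates of 90% down to 50%), and one for secondary objective 2 with n equal to the number referred. Say that the estimates by risk group will be less precise.
- State that 150 appointments assumes 15% meeting the criteria with full referral and attendance, and give the expected number under lower, explicitly assumed rates.
- Note that intervals may be wider because workers are recruited through companies, by an amount that depends on company size and ICC.

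Separately, confirm that company and OM-physician codes are captured. The Implementation science framework section (2.1.3) promises referral rates by both, and Table 2 lists neither.

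The cost is a few sentences and, if the codes are not already recorded, two coded fields, which are easiest to collect at enrolment. No endpoint or enrolment number changes.

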#### Recruitment

2.2.3

The involvement of local stakeholders (Unidade Local de Saúde de Entre o Douro e Vouga – ULSEDV, São João da Madeira City Council and São João da Madeira Commercial and Industrial Association) in the protocolization of a specific referral network for patients with elevated cardiovascular risk in the influence area of the ULSEDV, based on the universality and obligatory nature of Occupational Medicine consultations, was the adopted strategy for the identification of the participating companies and population’s recruitment.

#### Data collection

2.2.4

Participants will be assessed in three time points:
at baseline, at their working company by Occupational Safety and Health Technician and by OM doctorat T0, at hospital centre by a medical doctor, for participants referred by the OM doctor based on their CV-risk levelat T12, at hospital centre by a medical doctor, 12 months after T0.Study variables to be used in this study, and related definitions, are described in the following subsections. Table 2 shows the set of data that will be collected and variable features. The main study variables concern demographics, habits, laboratory testing, comorbidities, medications and destination are listed below in more detail.

**Table 2 T2:** Data collection – variables and corresponding features.

Variable	Label	Evaluation period
Inclusion Criteria Check		
consentimento_informado	Signed informed consent	Baseline
avaliacao_possivel	Participant willing and able to complete the assessments	Baseline
Demographics and disease history		
ano_de_nascimento	Birth year	Baseline
sexo	Sex	Baseline
tabagismo_status	Smoking status	Baseline, T0, T12
dieta	Enter Diet Data?^a^	Baseline
sono	On average, how many hours of sleep do you get in a 24-hour period?^b^	Baseline
exercicio_fisico	How many minutes of moderate (or greater) intensity activity per week?^b^	Baseline
drc_moderada_grave	Presence of Moderate or Severe Chronic Kidney Disease	Baseline, T0, T12
dm	Presence of Diabetes Mellitus	Baseline, T0, T12
historia_evento_cv	History of Cardiovascular Event	Baseline, T0, T12
especificacao_eventos_cv	Specification of Cardiovascular Events	Baseline, T0, T12
outros_antecedentes	Other Pathological History	Baseline, T0, T12
Diet Questionnaire		
dieta_porcoes_vegetais_semana	How many servings of vegetables do you consume per week?	Baseline
dieta_porcoes_carne_vermelha_semana	Servings of Red Meat per Week	Baseline
dieta_porcoes_manteiga_creme_semana	How many servings of butter or cream do you consume per week?	Baseline
dieta_porcoes_graos_integrais_dia	How many servings of whole grains do you consume per day?	Baseline
dieta_consumo_fastfood_semana	Times Consuming Fast Food Meals per Week	Baseline
por_es_de_frutas_por_semana	How many servings of fruit do you consume per week?	Baseline
dieta_peixe_semana	How many servings of fish or shellfish/seafood do you consume per week?	Baseline
dieta_feijoes_semana	How many servings of beans do you consume per week?	Baseline
dieta_doces_semana	How many servings of commercial sweets, candy bars, pastries, cookies, or cakes do you consume per week?	Baseline
dieta_bebidas_acucaradas_semana	How many servings of sugar-sweetened beverages do you drink per week?	Baseline
Usual Medication		
anti_dislipidemico	Anti-dyslipidemic	Baseline, T0, T12
anti_hta	Anti-hypertensive	Baseline, T0, T12
anti_agregantes	Anti-platelet	Baseline, T0, T12
farmaco_sem_medicacao	Without Usual Medication	T0, T12
farmaco_mh_dci	Drug (Previous Usual Medication) - International Nonproprietary Name (INN)	T0, T12
farmaco_mh_dose	Drug (Previous Usual Medication) - Dose	T0, T12
outro_farmaco	Insert another drug	T0, T12
Prescribed Medication		
intervencao	Was a new drug prescribed as a result of this assessment?	T0, T12
farmaco_intervencao_dci	Newly Prescribed Drug - International Nonproprietary Name (INN)	T0, T12
farmaco_intervencao_dose	Newly Prescribed Drug - Dose	T0, T12
outro_farmaco_intervencao	Insert another drug?	T0,T12
Clinical Evaluation		
ta_sist	Systolic Blood Pressure (mmHg)	Baseline, T0, T12
ta_diast	Diastolic Blood Pressure (mmHg)	Baseline, T0, T12
fc	Heart Rate (bpm)	Baseline, T0, T12
peso	Weight (kg)	Baseline, T0, T12
altura	Height (cm)	Baseline, T0, T12
Laboratory testing		
data_avaliacao_analitica	Date of Analytical Assessment	Baseline, T0, T12
colesterol_total	Total Cholesterol (mg/dL)	Baseline, T0, T12
ldl_c	LDL-C (mg/dL)	Baseline, T0, T12
hdl_c	HDL-C (mg/dL)	Baseline, T0, T12
triglicerideos	Triglycerides (mg/dL)	Baseline, T0, T12
hba1c	HbA1c (%)	Baseline, T0, T12
creatinina	Creatinine (mg/dL)	Baseline, T0, T12
egfr	Estimated Glomerular Filtration Rate (mL/min/1.73m^2^)	Baseline, T0, T12
ureia	Urea (mg/dL)	Baseline
lp_a	Lipoprotein (a)	T0
apo_a	Apolipoprotein A	T0, T12
apo_b	Apolipoprotein B	T0, T12
Destination		
destino_consulta_mo	Destination of the Participant	Baseline
destino_final_hospitalar	Destination After 12 Months of Hospital Follow-Up	T12
Medication adherence questionnaire		
qat_1_toma_hora	Do you always take your medication at the appropriate time?	T12
qat_2_sentir_mal	When you feel bad, have you ever discontinued taking your medication?	T12
qat_3_esquecer	Have you ever forgotten to take your medication?	T12
qat_4_esquecer_fds	Have you ever forgotten to take your medication during the weekend?	T12
qat_5_falha_semana	In the last week, how many times did you failed to take your prescribed dose?	T12
qat_6_dias_sem_medicacao	Since your last visit, how many whole days have gone in which you did not take your medication?	T12

a Indicates whether information about the participant's diet will be entered. This variable is mandatory for participants under 40 years old.

b Question from Life's Essential 8 questionnaire (14).

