6. Level of Adherence to Medication Prescribed in the Hospital CV Risk Consultation: Descriptive statistics will assess the adherence levels, measured by SMAQ among patients prescribed medications in the hospital CV risk consultations.
7. Proportion of Patients Who Attended Smoking Cessation Consultation: Descriptive statistics will determine the proportion of patients attending smoking cessation consultations over patients who were referred and participated in hospital CV risk consultation.
8. Change in distribution from Baseline in Various CV Risk Factors after 12 Months: Appropriate statistical methods will be used to calculate the distribution change from baseline (first hospital consultation) for the following CV risk factors after the use of this simplified referral process.
a. LDL-C
b. Blood pressure (SBP and DBP)
c. Moderate or severe chronic kidney disease
d. Smoking status
e. HbA1c
f. BMI
Statistical methods for this endpoint are specified in Section 2.3.1.
9. Distribution of Lipoprotein (a) at the first hospital consult: Descriptive statistics will assess the distribution of Lipoprotein (a) at the first hospital consult.
10. Prevalence of CV Risk Factors in the industrial/manufacturing in São João da Madeira: Appropriate statistical methods will be used to estimate the prevalence of CV risk factors within the industrial/manufacturing companies, including the levels of Lipoprotein (a) among very high CV risk individuals.
11. Proportion (%) of Identified Patients Referenced to GP Consultation: Descriptive statistics will be used to calculate the percentage of patients referred to GP consultations.

For the change in CV risk factors from baseline/T0 to T12, repeated continuous measures will be analyzed using linear mixed-effects models (or generalized estimating equations, as appropriate to the outcome distribution) with a random intercept per participant to account for within-subject correlation across the baseline, T0 and T12 assessments. Binary or categorical repeated measures will be analyzed using generalized estimating equations with a logit link. Models will be adjusted *a priori* for age, sex, baseline CV risk category, and baseline value of the outcome variable; additional covariates identified as clinically relevant confounders may be added in sensitivity analyses.

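### Three of the six T12 adherence items ask about lapses at any time, so in patients treated before T0 a lapse before the hospital consultation can count against endpoint 6.

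*Protocol article*

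**What the plan says.** Table 3 in section 2.3.1 names endpoint 6 as "Level of Adherence to Medication Prescribed in the Hospital CV Risk Consultation". It is measured with the SMAQ among patients who were prescribed medication there, and it serves secondary objective 3 (section 2.1.2), which looks at adherence 12 months after the intervention.

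Table 2 in section 2.2.4 lists six items, all collected at T12 only:

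- Item 1: "Do you always take your medication at the appropriate time"
- Item 2: "When you feel bad, have you ever discontinued taking your medication"
- Item 3: "Have you ever forgotten to take your medication"
- Item 4: "Have you ever forgotten to take your medication during the weekend"
- Item 5: "In the last week, how many times did you failed to take your prescribed dose"
- Item 6: "Since your last visit, how many whole days have gone in which you did not take your medication"

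Section 2.2.4 sets three assessments: baseline at the company, T0 at the hospital, and T12, which takes place "at hospital centre by a medical doctor, 12 months after T0". Section 2.2.13 says that the questionnaire is an adapted SMAQ. Section 2.3 says that the date of each visit is recorded.

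**The concern.** The endpoint concerns drugs prescribed at T0, so only behaviour after T0 can bear on it. Items 2 to 4 are tied neither to T0 nor to those drugs.

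Patients with earlier treatment are expected in the cohort. Table 2 records lipid-lowering, antihypertensive and antiplatelet drugs from baseline and previous usual drugs at T0. Section 2.2.1.1 applies the referral criteria whether or not there is prior atherosclerotic disease.

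For such a patient, a lapse from years before the consultation produces the same answer as a lapse last month. The reported adherence would then partly reflect how long patients had been on treatment before the pathway began. The questionnaire is given only once, so no earlier answer exists against which to net out old lapses. An undated answer also cannot be dated later, so an analysis plan cannot repair it.

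**Working it through.** **The plan's own figures.** The article gives no figure for adherence. Its only precision figure is a 2.2% margin for a prevalence of 15% in 1000 persons (section 2.2.2). It reproduces, 1.96 × √(0.15 × 0.85 / 1000) = 0.0221, but has no bearing here. The check is therefore mainly of wording against schedule.

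**Step 1. Recall period of each item, against the period from T0 to T12.**

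| Item | Period as worded | Can it count a lapse before T0? |
|---|---|---|
| 1 | none stated (general habit) | not stated |
| 2, 3, 4 | any time in the past | yes, if treated before T0 |
| 5 | last week | no |
| 6 | since the last visit | no: on the three-visit schedule the last visit is T0, and any later contact only shortens the period |

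Three of the six items can therefore reach back before T0.

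**Step 2. Who is affected.** For a patient first treated at T0, asking about any time in the past is in effect asking about the time since T0. Only patients who took medication before T0 are exposed to the problem.

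**Step 3. Direction.** With accurate recall, anyone who lapsed after T0 answers yes under either wording. The undated wording can only add yes answers from earlier lapses. The error goes against adherence.

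**Step 4. Illustration for one undated item.** All inputs are assumptions. Let p be the share with at least one lapse in the 12 months after T0, with the same constant lapse rate before T0, independence over time and full recall. With m treated months before T0:

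P(yes) = 1 − (1 − p)^((12 + m)/12)

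For p = 20%:

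- m = 0: 1 − 0.8 = 20%
- m = 24: 1 − 0.8³ = 1 − 0.512 = 48.8%
- m = 60: 1 − 0.8⁶ = 1 − 0.262 = 73.8%

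For p = 30% and m = 24: 1 − 0.7³ = 1 − 0.343 = 65.7%.

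If a share s of patients had 24 earlier months, the overall share answering yes is (1 − s) × p + s × P(yes | m = 24):

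| s | p = 20% | p = 30% |
|---|---|---|
| 0 | 20% | 30% |
| 25% | 27.2% | 38.9% |
| 50% | 34.4% | 47.9% |
| 75% | 41.6% | 56.8% |

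For example, at s = 50% and p = 20%: 0.5 × 0.20 + 0.5 × 0.488 = 0.344. If old lapses are forgotten, or if the same patients lapse in both periods, the excess is smaller.

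**The case against.** **Endpoint 6 is limited to drugs prescribed at T0, so for those drugs the undated items can only mean since T0.** This is right for patients with no earlier treatment. It does not cover the others, because the items as printed refer only to the patient's medication in general. Tying the answers to the T0 prescription would remove most of the problem, which is why the fix does so.

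**The form, its instructions and the scoring rule are not shown.** Table 2 gives labels, and an article commonly leaves the rest to the full protocol. An instruction line may already exist. For that reason the effect on the overall adherence level cannot be sized. The printed wording still carries no start date, and no scoring rule can recover one.

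**The wording belongs to a named questionnaire.** This is a fair argument against rewriting several items, or against replacing the overall result with items 5 and 6 alone. It weighs less against an instruction line on a version that section 2.2.13 already calls adapted.

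**The consequence is limited.** Endpoint 6 is descriptive, in a non-randomized pilot, and no comparison of adherence between patients is planned. This stands.

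**A stronger reading that a reader might infer.** One might group item 6 with items 2 to 4, as if it too admitted lapses from before the consultation or covered a different period in each patient. The documents do not support this. On the stated schedule it runs from T0, about 12 months for everyone. It would become shorter only if an unscheduled hospital contact or a smoking cessation consultation were taken as the last visit. Nor does Table 3 say that item 6 is reported as a raw count. What remains is that the last visit is not defined.

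**Conclusion.** The point holds for items 2 to 4 in patients who took medication before T0. In them a lapse before the consultation can be counted against adherence to what was prescribed at the consultation, and the reported adherence can only be lowered by this. It does not hold for patients first treated at T0. Items 5 and 6 are not affected in this way on the stated schedule.

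The size is open. On the assumptions shown, a single undated item would overstate the share with a lapse by 7.2 to 21.6 percentage points at p = 20% (27.2 − 20 and 41.6 − 20), and by nothing if nobody was treated earlier. These figures concern one item. They cannot be carried over to the overall adherence level, because the article gives neither the scoring rule nor the previously treated share. The change is still worth making: the bias runs one way, it cannot be removed once the answers are collected, and the remedy is one line on a form.

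**What to change.** Before the first T12 visit:

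1. Add one instruction line at the head of the T12 questionnaire, asking the patient to answer about the medication prescribed at the first hospital consultation and for the period since that consultation.
2. Define the last visit in item 6 as T0, on the form and in Table 2.
3. Optionally, report item 6 as missed days divided by the days from T0 to T12. The visit dates needed are already recorded.

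The cost is one revision of the form and a short note in Table 2. The downside is slightly less comparability with other uses of the SMAQ. The item wording itself can stay.
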